## Abstract

*Background and Objectives:* Trigger points (TrPs) are prevalent in patients with migraine headaches. Needling interventions targeting TrPs in migraine patients may reduce the intensity and frequency of headaches, yet systematic reviews reveal a lack of robust evidence. Intramuscular electrical stimulation (IMES) is a modality that delivers electrical current into muscles and TrPs, with recent studies suggesting it may amplify the therapeutic effects of dry needling peripherally and centrally. This could be advantageous for patients with migraine and symptomatic TrPs. *Materials and Methods:* This study will implement a multiple baseline single-case experimental design (SCED). In a clinical setting, a SCED study lends itself to conducting research with only a few patients that each serve as their own controls. In this SCED study, four participants with chronic migraine will be enrolled in a non-concurrent manner and randomized to one of four baseline measurement periods (4, 5, 6 or 7 weeks), leading to four potentially different start dates for each participant in the intervention phase. During the intervention phase, patients will receive five sessions of dry needling with IMES, one session per week for five weeks. The primary outcome measure will be headache frequency, i.e., the reduction in the number of headache days over a one-month period using electronic headache diary data from the Migraine Buddy smartphone application. Secondary outcome measures will be changes in mean migraine pain intensity using a numeric pain rating scale (NPRS), migraine disability using the Migraine Disability Assessment Test (MIDAS), the Headache Impact Test (HIT-6), and changes in selected cervical musculoskeletal impairments including pressure pain thresholds (PPTs) over TrPs, the craniocervical flexion test (CCFT), and cervical active range of motion (AROM). Primary and secondary outcome measures will be analyzed separately using both visual and statistical analyses. *Results*: Actively recruiting participants. This project was approved by the Mass General Brigham Institutional Review Board (protocol #2023P000931) and is registered with ClinicalTrials.gov (NCT05893914). *Conclusions*: This study will seek to determine the effects of a five-week intervention period of IMES to TrPs in the posterior cervical muscles of subjects with chronic migraine.

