## 2. Methods

### 2.1. Study Design

This study protocol and subsequent experiment will follow the Single-Case Reporting Guideline in Behavioral Interventions (SCRIBE) 2016 [35]. This project was approved by the Mass General Brigham Institutional Review Board (protocol #2023P000931) and is registered with ClinicalTrials.gov (NCT05893914). This study will implement a single-case, non-concurrent, multiple-baseline experimental design, using an AB design (A = baseline, B = treatment). To strengthen the internal validity of this experiment, participants will be randomly assigned to one of four baseline tiers, leading to four potentially different start dates for each participant in the intervention phase. The first tier will include 4 weeks (28 days) of baseline measurements (phase A), followed by 5 weeks of treatment and symptom monitoring (phase B); the second tier will include 5 weeks (35 days) of baseline measurements (phase A), followed by 5 weeks of treatment and symptom monitoring (phase B); the third tier will include 6 weeks (42 days) of baseline measurements, followed by 5 weeks of treatment and symptom monitoring (phase B); and the fourth tier will include 7 weeks (49 days) of baseline measurements, followed by 5 weeks for treatment and symptom monitoring (Figure 1). According to the International Headache Society, a 28-day minimum prospective baseline period using a headache diary is recommended to establish the attack frequency in a study of chronic migraine [36]. The length of the baseline and follow-up periods were chosen to ensure a minimum of 4 to 5 assessments per participant per phase, as recommended for the analyses of SCEDs [31]. In total, the duration of the study will be 9–12 weeks depending on the baseline assignment. In the intervention phase (phase B), all participants will receive one intervention session per week, over five weeks.

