### 2.6. Outcome Measures

#### 2.6.1. Primary Outcome Measure

For this study, the reduction in headache frequency, which is the reduction in the number of headache days over a one-month period, will be the primary outcome measure [71]. The primary end point for this study is the 6th, and final, visit at the end of the intervention phase where the change in the headache frequency will be assessed. Headache diary reports will be sent to the principal investigator each week during the baseline and intervention periods of the study. The headache diary reports will be sent through a secure electronic patient portal as a PDF report generated through the Migraine Buddy smartphone application. Use of this application for research purposes has increased in recent years to capture headache data and for outcome monitoring [72,73]. Headache characteristics, triggers, and medication use will also be recorded in the headache diary with a time stamp feature for data collection in real time. All headache diary data will be analyzed and stored on a Microsoft Excel spreadsheet, with all participant information de-identified. A migraine day will be defined as a day with a headache that lasts at least 4 h, which meets the International Classification of Headache Disorders 3rd edition criteria for migraine without aura, migraine with aura, and probable migraine, or a day with a headache that is successfully treated with migraine-specific acute medication [36].

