#### 2.6.2. Secondary Outcome Measures

Secondary outcome measures will include the Headache Impact Test-6 (HIT-6) and the Migraine Disability Assessment Test (MIDAS). The HIT-6 is a six-item questionnaire assessing headache severity and change in a participant’s clinical status over a short period of time (4 weeks) [74]. The MIDAS is a self-administered questionnaire designed to quantify headache-related disability over a 3-month period [75]. Changes in PPTs to TrPs that correlate with migraine headache symptoms will also be analyzed [43,76]. In addition, changes in cervical musculoskeletal impairments with AROM, and performance on the CCFT will be measured. Lastly, the reduction in average headache pain intensity over a 1-month period will be assessed using the Numerical Pain Rating Scale (NPRS). The NPRS is used to rate the intensity of the headache pain. It is a scale featuring 11-points, with 0 indicating no pain and ten indicating pain as intense as one could imagine. The NPRS has been validated for use in measuring migraine severity [77]. The mean headache intensity will be calculated by dividing the sum of all NPRS scores on headache days and the mean of all noted headache days.

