### 2.9. Adverse Events and Monitoring

Monitoring for adverse events (AEs) will be performed at each treatment visit by the principal investigator and will be recorded on the participants’ behalf using the headache diary. Participants will be given an informative handout describing what steps to take in the event of an adverse reaction to dry needling, and participants will be advised to immediately seek medical attention and notify the principal investigator and their physician. Possible minor side effects of dry needling may include temporary pain during needling, numbness or tingling, minor bleeding, bruising, drowsiness, tiredness, dizziness, and possible fainting [82]. More significant adverse events include pneumothorax and cervical epidural hematoma [83,84]. However, none of the muscles selected for treatment in this study are in proximity to the lung field. If a subject demonstrates an increase in the average headache pain intensity of more than two points on the NPRS following the first week of treatment or if a subject reports an increased number of consecutive headache days above their reported weekly average, the principal investigator will consult the patient and recommend discontinuation of the study.

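### Section 2.6.2 divides the NPRS sum by a mean of headache days instead of their number, so on most literal readings the intensity outcome is not a mean NPRS score

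*Protocol article*

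**What the plan says.** Average headache intensity is a secondary outcome. The Abstract lists "changes in mean migraine pain intensity using a numeric pain rating scale (NPRS"), and section 2.6.2 sets the time frame: "the reduction in average headache pain intensity over a 1-month period will be assessed using the Numerical Pain Rating Scale (NPRS"). The same section bounds the scale: "It is a scale featuring 11-points, with 0 indicating no pain and ten indicating pain as intense as one could imagine".

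Section 2.6.2 then gives the calculation, the only one in the article: "dividing the sum of all NPRS scores on headache days and the mean of all noted headache days". It does not say what the mean is taken over.

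Three other statements bear on how that sentence could be read:

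- Section 2.6.1, on data flow: "Headache diary reports will be sent to the principal investigator each week during the baseline and intervention periods of the study".
- Section 2.1, on phase lengths: "The first tier will include 4 weeks (28 days) of baseline measurements (phase A), followed by 5 weeks of treatment and symptom monitoring". The other tiers have 5, 6 and 7 weeks of baseline, each followed by 5 weeks of treatment.
- Section 2.9, on monitoring, which acts on "an increase in the average headache pain intensity of more than two points on the NPRS following the first week of treatment" and does not refer to the calculation in 2.6.2.

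**The concern.** An average score per headache day is the total of the scores divided by how many such days there were. The sentence in 2.6.2 puts a mean of headache days in the place of that count. A mean of days must be taken per something, and the unit is left open. Whoever builds the spreadsheet has to supply it, and different choices give different outcomes.

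Two things are at stake. First, the result may not lie on the NPRS at all, so it cannot be read as pain intensity. Second, it may carry information about how often headaches occur. Frequency is the primary outcome, and the intensity outcome is meant to add something separate from it.

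This is not a detail deferred to an unseen analysis plan. The article states a formula for a named outcome, and the formula is wrong as stated.

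**Working it through.** The documents give no numerical value for this outcome, so there is nothing to reproduce. The check is algebra.

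**Inputs from the protocol article:** NPRS from 0 to 10 (2.6.2); one-month period (2.6.2); baseline of 4, 5, 6 or 7 weeks and treatment phase of 5 weeks (2.1); weekly diary reports (2.6.1); at least 15 headache days a month at entry (2.3.1).

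**Assumed for illustration:** a constant score m = 6 on every headache day, and d headache days per week, the same in both phases (d = 4, 5 and 6 were tried). Over w weeks the NPRS sum is m × d × w.

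**1. Correct divisor.** The number of headache days is d × w, so the mean is m·d·w / (d·w) = m = 6.0 for every phase length and every d.

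**2. One 28-day window, literal wording.** Take d = 4, so the sum is 6 × 4 × 4 = 96.

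- Divisor is the weekly mean of headache days: 96 / 4 = 24, which is impossible on a scale that ends at 10.
- Divisor is the 28-day figure, which is then the single count for that month: 96 / 16 = 6.0, which is correct.

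Because d cancels, d = 5 and d = 6 give the same two results.

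**3. Weekly points, divided by the phase's mean weekly headache days.** Section 2.1 wants at least 4 to 5 assessments per phase, so weekly points are plausible. Take four weeks with 3, 5, 4 and 4 headache days; the mean is 16 / 4 = 4.

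| Week | Headache days | NPRS sum | Sum / 4 | Sum / own count |
|---|---|---|---|---|
| 1 | 3 | 18 | 4.5 | 6.0 |
| 2 | 5 | 30 | 7.5 | 6.0 |
| 3 | 4 | 24 | 6.0 | 6.0 |
| 4 | 4 | 24 | 6.0 | 6.0 |

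Intensity never changed, yet the literal value ranges over 7.5 - 4.5 = 3 points and moves exactly with frequency.

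**4. Conditional case: sums over whole phases.** The quotient is m × w with a weekly mean as divisor and m × w / 4 with a 28-day mean.

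| Baseline | A, weekly mean | B, weekly mean | A, 28-day mean | B, 28-day mean | Change with no true effect |
|---|---|---|---|---|---|
| 4 weeks | 24 | 30 | 6.0 | 7.5 | +25% |
| 5 weeks | 30 | 30 | 7.5 | 7.5 | 0% |
| 6 weeks | 36 | 30 | 9.0 | 7.5 | -17% |
| 7 weeks | 42 | 30 | 10.5 | 7.5 | -29% |

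The percentages are (5 - w) / w, for example (30 - 42) / 42 = -28.6%. With a fixed 28-day window in each phase, as in step 2, both phases give the same value (24 and 24, or 6.0 and 6.0) and the tier effect disappears.

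**The case against.** The strongest reply is that the sentence is a slip rather than a formula anyone would apply. It is ungrammatical, the outcome is called a mean or an average throughout, and the scale is bounded at 10. The independent statistician named in section 2.8 would notice a score of 24 or 42. The one-month period in the same section also suggests that sum and divisor cover one period, in which case the supposed mean is a single count and the answer is right. The weekly unit comes from a reporting schedule, not from an outcome definition.

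Much of this stands, and it limits the point in three ways.

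- A reader might infer that the outcome is bound to change with the randomized baseline length. The documents do not support that. It needs sums over whole phases, which no section states and which the one-month period contradicts. Even then the 5-week tier shows no shift.
- A reader might infer that most values would leave the 0 to 10 scale. That holds for a weekly mean as divisor. With a 28-day mean, only the 7-week baseline value of 10.5 in step 4 exceeds 10.
- A reader might infer that the wording disables the monitoring criterion in section 2.9. That section speaks of points on the NPRS and does not invoke the calculation in 2.6.2, so this cannot be concluded.

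The reply does not remove the error. No other sentence corrects the divisor. The harmless reading is possible but not secured: the month is not located within each phase, and only the first tier's baseline is exactly 28 days long. Nor would every misreading be caught by eye, since 4.5 and 7.5 in step 3 look like ordinary pain scores.

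**Conclusion.** The divisor in 2.6.2 is wrong as written and should be corrected. On most literal readings the quotient is not a mean NPRS score: 24 in place of 6 over 28 days with a weekly mean, or weekly values from 4.5 to 7.5 at constant intensity 6 when they are scaled by a phase mean. One reading, a single month's count, gives the correct 6.0.

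The illustrations rest on an assumed constant score of 6 and, in steps 2 and 4, a constant frequency; in those two steps the number of headache days per week cancels. The tier-dependent changes of +25%, 0%, -17% and -29% apply only if whole phases were summed, and are not an established consequence of the plan.

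The weight is modest. This is one secondary outcome in an exploratory study of four participants, and the primary outcome, headache days, does not use the formula.

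**What to change.** Replace the sentence in 2.6.2 with:

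> Mean headache intensity in a period is the sum of the daily NPRS scores on headache days divided by the number of headache days in that same period.

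State which one-month window is used in the baseline and in the treatment phase. If weekly values are also plotted or modelled, use each week's own sum and own count.

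Reconcile the average intensity mentioned in section 2.9 with this definition, so that the term has one meaning in the article. The clinical rule itself is left as it is.

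The cost is one protocol sentence, the naming of the window, and one formula in the diary spreadsheet. No new data are needed. With the corrected divisor, unchanged pain of 6 gives 6.0 in every tier and both phases.

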### 2.7. Data Analysis

#### 2.7.1. Visual Analysis

In this SCED study, the primary and secondary outcome measures will be analyzed separately using both visual and statistical analyses. First, we will conduct an exploratory data analysis to observe within- and between-phase patterns in the data with emphasis on level (mean score for the data), trend (slope), variability (spread of data points), and overlap (calculation of points overlapping between phases) [29,31,78]. The stability of data points will be assessed following the completion of the baseline phase [78]. Individual participant data will be represented using data visualization methods, including a graphical plot for each outcome variable both within and across participants. Non-overlap indices will be used to further assess overlap and will include non-overlap of all pairs (NAP) or the baseline-corrected Tau-U, depending on the baseline trend [79]. In addition, NAP, or baseline-corrected Tau-U will be used to measure effect size [31,80].

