#### 2.7.2. Statistical Analysis

A longitudinal mixed-effects statistical model (also referred to as hierarchical or multilevel modeling) will be used to analyze the overlap between baseline to post-intervention for all outcome measures [81], provided that the data allows for such an analysis. A mixed-effects model can account for individual differences through the inclusion of random effects and is known to have increased statistical power by its ability to use all available data points.

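### The primary outcome is a reduction in headache days, but the only measure designated as effect size is a non-overlap index, and no estimate in days is named as the effect

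*Protocol article*

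**What the plan says.** Section 2.6.1 fixes the scale of the primary outcome: "the reduction in the number of headache days over a one-month period, will be the primary outcome measure". It also fixes the time: "The primary end point for this study is the 6th, and final, visit at the end of the intervention phase", when the change in frequency is to be judged. Diary reports arrive weekly through both phases.

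Section 2.7.1 begins with an exploratory visual step, with "emphasis on level (mean score for the data), trend (slope), variability (spread of data points), and overlap (calculation of points overlapping between phases"). It then names the overlap indices, "non-overlap of all pairs (NAP) or the baseline-corrected Tau-U, depending on the baseline trend", and gives them a second role: "In addition, NAP, or baseline-corrected Tau-U will be used to measure effect size". The article calls nothing else an effect size.

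Section 2.7.2 says that a longitudinal mixed-effects model "will be used to analyze the overlap between baseline to post-intervention for all outcome measures", "provided that the data allows for such an analysis". It states no contrast in days as the model's result.

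Four participants are "randomized to one of four baseline measurement periods (4, 5, 6 or 7 weeks"), and each then has five treatment weeks (Abstract and Section 2.1).

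**The concern.** The outcome has a unit, days per month. The designated effect size has none. NAP is the proportion of all baseline–treatment pairs in which the treatment value is the better one, with ties counted as half. It records how consistently values fall, not how far. Two features follow when it is applied to weekly counts. Once every treatment week is below every baseline week, the index is at its maximum whatever the distance between the phases. Short of that, it reflects week-to-week spread as well as the reduction.

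With four participants, the individual results are the main output. If the number labelled effect size is the one carried into an abstract or a later evidence summary, it may not show how many headache days were removed, and it may order participants differently from their reductions.

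**Working it through.** The article gives no weekly counts, variances or target reduction, so there is no planned figure to reproduce. The series below are constructed. They use the first tier (4 baseline and 5 treatment weeks, Section 2.1), counts from 0 to 7 per week, and baselines above the eligibility floor of 15 headache days per month (Section 2.3.1).

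**Formulas.**
- NAP = [pairs with A > B + 0.5 × pairs with A = B] / (nA × nB), where A is a baseline week and B a treatment week. Here nA × nB = 4 × 5 = 20.
- Fall in days per 28 = 4 × (mean weekly count in A − mean weekly count in B).

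**1. Saturation.** Baseline 5, 5, 6, 5 (mean 5.25).
- Then 4, 4, 4, 4, 4: NAP = 20/20 = 1.00; fall = 4 × (5.25 − 4) = 5 days.
- Then 0, 0, 0, 0, 0: NAP = 20/20 = 1.00; fall = 4 × 5.25 = 21 days.

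A rank correlation of phase with outcome behaves the same way. Baseline 5, 5, 5, 5 has no trend to correct. Followed by all 4 (fall of 4 days) or all 1 (fall of 16 days), it gives Kendall's tau-b of −1.00 in both cases.

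**2. Order reversed.**

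| Baseline | Treatment | Fall per 28 days | NAP |
|---|---|---|---|
| 7, 7, 7, 7 | 6, 6, 6, 6, 6 | 4 × (7 − 6) = 4 | 20/20 = 1.00 |
| 6, 3, 7, 4 | 4, 2, 3, 5, 1 | 4 × (5 − 3) = 8 | 16/20 = 0.80 |
| 5, 5, 5, 5 | 4, 4, 4, 4, 4 | 4 × (5 − 4) = 4 | 20/20 = 1.00 |
| 7, 4, 7, 4 | 5, 1, 4, 1, 4 | 4 × (5.5 − 3) = 10 | 16/20 = 0.80 |

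In the second row, the baseline weeks 6, 3, 7 and 4 contribute 5, 2.5, 5 and 3.5 pairs, in total 16. In the fourth row, the weeks contribute 5, 3, 5 and 3, again 16.

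**3. Dependence on spread.** As a rough guide, suppose weekly counts are normal with equal SD in both phases (an assumption, crude for counts capped at 7). Then NAP = Φ[δ / (SD × √2)], with δ the weekly fall.

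| Fall per 28 days | Weekly SD | Expected NAP |
|---|---|---|
| 4 | 0.5 | 0.92 |
| 4 | 1 | 0.76 |
| 8 | 1 | 0.92 |
| 8 | 2 | 0.76 |
| 12 | 2 | 0.86 |

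A 4-day fall with SD 0.5 scores the same as an 8-day fall with SD 1, and higher than a 12-day fall with SD 2.

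**4. Daily instead of weekly values.** Code each day 1 (headache) or 0, with proportions pA and pB. Then NAP = pA(1 − pB) + 0.5[pA·pB + (1 − pA)(1 − pB)] = 0.5 + 0.5(pA − pB). This is linear in headache days. Falls of 5 and 21 days per 28 give 0.5 + 0.5 × 5/28 = 0.59 and 0.5 + 0.5 × 21/28 = 0.88. There is no reversal, and the maximum is reached only by going from headache every day to none. Steps 1 to 3 therefore depend on weekly aggregation.

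**The case against.** The strongest reply is that days are in the plan already. The outcome is defined in days, the change in frequency is assessed at the final visit, level is the first feature listed for the visual step, and every outcome is plotted for each participant. A fall of 5 days and a fall of 21 days would look different on those plots. That stands. A reader might infer that the trial cannot say how far headache days fall, and the article does not support that. What is missing is the designation: the phase mean is a feature to inspect, while the index is what the plan calls the effect size.

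Second, a mixed model does not literally analyse overlap, and its phase term for headache frequency would naturally be in days or a rate, so the wording may be a slip. The exact contrast could sit in a statistical analysis plan that is not shown. This is fair and lowers the weight of the point. But the article does not merely leave the target open; it states one, and that target is not the primary outcome. The model is also conditional.

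Third, non-overlap indices are an accepted supplement in single-case research. Agreed, and there is no reason to remove them.

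Fourth, the weekly basis is not stated, and on daily values NAP has none of these faults. This also stands as a condition. Weekly is the likelier reading because Section 2.1 justifies the phase lengths by a minimum of four to five assessments in each phase, which fits weeks and not the 28 to 49 baseline days.

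A reader might also infer that the randomised baseline length itself shifts the Tau-U score. The article gives no formula for its baseline correction, and variants differ, so no figure for such an effect can be supported.

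**Conclusion.** The point holds in a limited form. The only quantity named as effect size does not measure the primary outcome on its own scale, and the description of the mixed model repeats the mismatch. On weekly counts, the consequence can be large in individual cases: the same NAP of 1.00 for falls of 5 and 21 days per 28, and 1.00 for a 4-day fall against 0.80 for an 8- or 10-day fall. These figures come from constructed series, some with no week-to-week variation at all. They show what the index can do, not how often it will do so here. They assume weekly aggregation, which the article does not state.

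This is a cheap and worthwhile correction to an exploratory study of four people. It is not a reason to think that the primary question will go unanswered, since phase means and plots are planned.

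**What to change.** - **Section 2.7.1:** name as the effect estimate for headache frequency each participant's headache days per 28 days in phase A minus phase B, with each phase total divided by its length in days and multiplied by 28. In the first saturation example this is 21/28 × 28 − 20/35 × 28 = 21 − 16 = 5 days. Report all four values and their average. These need no model, so they remain available if the mixed model cannot be fitted.
- **Section 2.7.2:** reword so that the mixed model estimates this same difference in headache days, with its interval, in place of overlap.
- **NAP or Tau-U:** keep as supplementary descriptors of overlap, and state whether they are computed on weekly or daily values.

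The cost is a few sentences of wording and one further column in the results table, from diary data already collected. The downside is that, with four participants and few weekly points, the intervals will be wide, and visibly so.
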